#### LLIN durability and bio-efficacy

Durability and bio-efficacy of the LLINs will be assessed 1 year after the distribution of nets, concurrently with the 12-month cross-sectional survey. We will quantify net durability and bioavailability of insecticides using standard WHO methodologies. To assess LLIN durability (the number, location, size, and type of holes in each net), a sub-set of nets distributed during the 2016–2017 universal LLIN campaign will be withdrawn (and replaced) from households during the 12-month cross-sectional survey. We propose to sample 400 nets (100 per study arm) from randomly selected households using the list of households selected for the cross-sectional community surveys. During the cross-sectional survey, availability of nets distributed during the 2016–2017 universal LLIN campaign will be assessed in selected households. If nets are available in the household, one net per household will be withdrawn (and replaced) for the durability assessment. We will quantify durability of the net using the methodology developed by the WHO Vector Control Working Group [33].

To assess LLIN bio-efficacy (the degree of knock-down, mortality, or inhibition of blood-feeding induced in susceptible mosquitoes, as determined by cone bioassays), the sub-set of 400 nets will also undergo bio-efficacy assessments. We will use a standard laboratory strain of *An. gambiae* from Kisumu, Western Kenya, which is fully susceptible to both permethrin and deltamethrin in WHO discriminant dose tests. In brief, five unfed 3- to 5-day-old mosquitoes will be exposed for 3 min to a net sample taken from the top of each net. The rationale being that this is the first point of contact for a mosquito taking a blood meal and ensures that we sample the dual treated surface on both types of PBO net [34, 35]. Knock-down will be recorded 60 min post-exposure and mortality after 24 h. Two net samples will be used per net and five cone tests will be conducted per sample together with appropriate negative controls. For a subset of 20 nets of each type we will use the same protocol but with a Ugandan pyrethroid resistant strain which exhibits P450-mediated resistance to test for the durability of PBO treatment on the dual-treatment nets.

### Laboratory procedures

#### Microscopy

Thick blood smears will be made by placing a drop of blood in the middle of a barcoded slide. Slides will be dried and kept in the field for no longer than 7 days to avoid auto-fixation. While in the field, slides will be stored in a cool environment and protected from excess heat and sunlight. Blood samples will be transported periodically to the Infectious Diseases Research Collaboration (IDRC) Molecular Research Laboratory (MOLAB) in Kampala for reading. At the MOLAB, thick blood smears will be stained with 2% Giemsa for 30 min and then evaluated for the presence of parasitaemia (asexual forms only). A thick blood smear will be considered negative when the examination at 100× high-power fields does not reveal asexual parasites. For quality control, all slides will be read by a second microscopist. If there is a discrepancy between the first and second reads (defined as any of the following: 1) a positive versus negative for asexual parasites, 2) parasite density differing by ≥ 25%, and 3) positive versus negative for gametocytes), a third microscopist will review the slide.

#### Haemoglobin measurement

Haemoglobin analysis will be carried out in eligible children 2–4 years of age on site using a drop of blood collected from a finger-prick using a battery-operated portable analyser (HemoCue, Anglom, Sweden). Any participant who is found to have severe anaemia (haemoglobin < 7.0 g/dL) requiring treatment will be referred to an appropriate healthcare facility for further management.

#### Filter paper samples

Blood spots will be collected onto filter paper to store for future serologic and/or molecular studies which will be performed only for research purposes and will have no impact on the clinical management of study participants. Filter paper (Whatman no 1, Whatman 3MM; Whatman, Maidstone, UK) will be pre-cut into individual squares, stapled to a thick card which will serve as its cover, and will be labelled with a barcode. Blood spots will be collected onto the filter paper in volumes of approximately 25-μl aliquots per blood spot (four blood spots per sample). Filter paper samples will be allowed to dry at ambient temperature and relative humidity, transported from the field in a zip lock bag, and will be placed into a stock card filter paper box for final storage with a desiccant.

#### Rapid diagnostic tests

RDTs (SD Bioline Malaria Ag P.f or P.f/Pan, Standard Diagnostics, Inc.) will be performed in the field on cross-sectional survey participants who are found to have a temperature ≥ 38.0 °C or who report fever in the past 48 h. RDTs will be performed according to the directions provided for the specific tests, using the blood transfer device and reagent provided by the manufacturer. Tests will be performed by study personnel, and results will be available within 15 min. The results of the RDT will be provided to the participant’s caregiver verbally and will be recorded on the appropriate case record form. Participants who test positive for malaria will be provided with a full course of anti-malarial treatment and will also be counselled to go to the nearest healthcare facility immediately if their condition worsens.

#### Insecticide resistance monitoring

We plan to use a combination of single nucleotide polymorphisms in the P450 *Cyp4j5* and the esterase *Coeae1d* which were reproducibly associated with pyrethroid resistance in multiple field collections from Uganda and Kenya, and which together with the *Vgsc*-1014S (kdr) mutation explained around 20% of variation in pyrethroid resistance [17]. These will be supplemented by Ugandan-specific resistance markers identified through the *Anopheles gambiae* 1000 genomes project (Ag1000G), and allied projects [30, 36]. Female anopheles mosquitoes collected from the 104 clusters during the entomology surveys will be identified and will be stored and refrigerated in the field sites prior to shipment to Kampala and onto LSTM for further analysis.

### Data management

All data will be collected by survey teams using hand-held tablet computers. Prior to conducting the surveys, information from the questionnaires and fields for entering results of laboratory testing will be programmed into the tablet computers. Programming will include range checks, structure checks, and internal consistency checks. Before leaving the household, an inventory will be made of the completed questionnaires and blood samples collected; both will be checked to make sure they are labelled correctly. The completed questionnaires will be checked for mistakes and completeness. Data from these devices will be transferred at the end of every day to our data core facilities in Kampala and stored on a secure server. The data file will be kept on a separate network so that only authorized survey staff will have access to the data during collection and the processing phase. The file with data from the questionnaires will be merged with results from reading the malaria slides at the laboratory, using the unique bar codes. All filter paper samples and blood slides will be returned to the IDRC offices in Kampala.

Laboratory data, including results of microscopy, will be recorded by study personnel on standardized data forms. Data entered onto paper record forms will be entered into a computerised database (Microsoft Access) by a data entry clerk and will be double-entered to verify accuracy. An audit trail of the date and time of data entry, and a record of any changes made, will be kept in compliance with Good Clinical Practice (GCP). All study personnel will be trained in the project objectives, methods of effective communication with study participants, collection of high-quality data, and principles of ethical research practice. Study personnel members will receive additional training specific to the tasks they will perform within the project including interviewing techniques, administration of surveys, completing questionnaires, and use of tablet devices. Standard operating procedures (SOPs) will be written for all project activities, and booklets of all relevant documents provided to each member of the project team.

Records for this study will be maintained and stored in compliance with the principles of GCP and regulatory and institutional requirements, and in compliance with the requirements for the protection of confidentiality of participants.

### Sample size calculations

#### Community surveys

The study sample size (number of clusters and allocation of interventions) was set by the number of nets available for the four different types of study nets and the estimated number of LLINs required per cluster. We will sample all eligible children aged 2–10 years from 50 households in the 104 clusters in each round of surveys, resulting in an estimated total of 10,400 children from 5200 households per survey. Assuming a parasite prevalence of 40% in the control arm [25], and coefficient of variation between clusters of 0.3 (derived from the ongoing trial in Tanzania [21]), we will have 80% power (two-sided significance level of 0.05) to detect a relative reduction in parasite prevalence of at least 17% (prevalence ratio of 0.83).

#### Entomology surveys

We aim to collect 30–50 mosquitoes per cluster. The sample sizes were chosen based on the expected frequency (50 to 60%) of the known resistance-associated P450 variant (*Cyp4j5*) in Eastern Uganda [17]. Therefore, a relatively small sample size is required for an accurate estimate of resistance marker frequency. However, we are aware that resistance is a highly dynamic system and that we may need to increase the number of mosquitoes analysed in certain clusters if resistance marker frequencies change dramatically.

### Analytical issues

#### Primary and secondary outcomes

The primary and secondary outcomes are outlined in Table 2.

**Table 2 Tab2:** Outcome measure definitions

	Indicator definition
Community survey	
Prevalence of parasitaemia	Proportion of thick blood smears that are positive for asexual parasites
Prevalence of anaemia	Proportion of haemoglobin measurements categorized as anaemia (< 10.0 g/dL)
LLIN coverage	Proportion of households owning at least one net
	Proportion of households owning at least one LLIN
	Average number of nets per household
	Average number of LLINs per household
	Proportion of households with one LLIN for every two residents
	Proportion of children who slept under an LLIN the prior night
	Proportion of pregnant women who slept under an LLIN the prior night
Insecticide resistance	
Phenotyping	Prevalence of phenotypic insecticide resistance
Genotyping	Prevalence of molecular markers associated with insecticide resistance
LLINs	
Survivorship	Proportion of households owning at least one 2016–2017 campaign net
	Proportion of households using at least one 2016–2017 campaign net the prior night
Durability	Proportionate Hole Index (PHI):
	1) good, 2) serviceable (repairable), or 3) in need of replacement
Bio-efficacy	Knock-down rate at 60 min of mosquitoes tested
	Mortality rate of mosquitoes tested

*LLIN* long-lasting insecticidal net

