In 2017–2018, the Ugandan Ministry of Health distributed LLINs with and without PBO through a national mass-distribution campaign, providing a unique opportunity to rigorously evaluate PBO LLINs across a variety of malaria transmission intensities, vector ecologies, and insecticide resistance patterns. In close collaboration with the Ministry of Health, we are conducting a cluster-randomised trial to evaluate the community-level impact of the LLINs delivered in the 2017–2018 national campaign at an unprecedented scale in Eastern and Western Uganda. This innovative, evaluation approach could be adopted for future assessments of malaria control interventions.

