### Secondary objectives and hypotheses

In addition, the following secondary objectives will be addressed:To evaluate the impact of PermaNet 3.0 (with PBO) compared with PermaNet 2.0 (without PBO) on parasite prevalence. We will test the hypothesis that parasite prevalence will be lower in intervention clusters (PermaNet 3.0 nets) than in control clusters (PermaNet 2.0 nets).To evaluate the impact of Olyset Plus (with PBO) compared with Olyset Net (without PBO) on parasite prevalence. We will test the hypothesis that parasite prevalence will be lower in intervention clusters (Olyset Plus nets) than in control health clusters (Olyset Nets).To determine the factors associated with the effectiveness of combination LLINs (with PBO) compared with conventional LLINs (without PBO), with a focus on the level of pyrethroid resistance. We will test the hypothesis that LLINs with PBO will be more effective than LLINs without PBO in settings with higher frequencies of P450-mediated pyrethroid resistance.To assess net durability, bio-efficacy, survivorship, and use. We will conduct cross-sectional surveys to determine net survivorship and use, and to measure attrition, and will supplement these with laboratory assessments of net durability and bio-efficacy.

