### Study design

The study includes 104 health sub-districts from 48 districts in Eastern and Western Uganda. The unit of randomisation is one health sub-district (cluster). Clusters were randomly assigned to receive one of four types of LLINs, including two LLINs with PBO: 1) PermaNet 3.0 (*n* = 32) and 2) Olyset Plus (*n* = 20); and two LLINs without PBO: 3) PermaNet 2.0 (*n* = 37) and 4) Olyset Net (*n* = 15). Prior to distribution of the nets, baseline surveys of community households and children aged 2–10 years, and entomological surveillance for insecticide resistance monitoring, were conducted (Fig. 1). LLINs were distributed within the study area by the Ministry of Health between March 2017 and March 2018. The evaluation includes follow-up community and entomology surveys at 6, 12, and 18 months post-distribution, plus assessment of net durability and bio-efficacy at 12 months. The primary outcome of the trial is parasite prevalence, measured by microscopy in children aged 2–10 years in the follow-up community surveys.

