## Trial status

The baseline community and entomology surveys were carried out from March to June 2017. LLINs were distributed in the study area between March 2017 and March 2018. The first round of follow-up surveys (6 months) started in September 2017 and the final round of surveys (18 months) are scheduled to complete in September 2019. We are seeking funding for an additional round of surveys, which would be conducted at 24–30 months following distribution of the LLINs.

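### Table 2's survivorship outcome is a household coverage measure that compresses net-level loss, and its campaign label does not match the campaign evaluated

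*Protocol article*

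**What the plan says.** Under Secondary objectives and hypotheses, the protocol article says that the cross-sectional surveys are meant "to determine net survivorship and use, and to measure attrition". Table 2 (Primary and secondary outcomes) then gives two survivorship indicators: "Proportion of households owning at least one 2016–2017 campaign net" and "Proportion of households using at least one 2016–2017 campaign net the prior night". Both take the household as the unit, need only one net, and do not restrict the denominator to households that received campaign nets.

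The LLIN distribution section sets the number of nets per household at half the number of residents, rounded up. The section on follow-up surveys says that households are drawn afresh for each round, and that the questionnaire will be adapted to ask about the campaign nets.

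On dates, the Background says that the trial will "evaluate the community-level impact of the LLINs delivered in the 2017–2018 national campaign". Study design states: "LLINs were distributed within the study area by the Ministry of Health between March 2017 and March 2018". Trial status repeats those dates. Table 2 and the section LLIN durability and bio-efficacy instead label the nets 2016–2017; the durability section refers to "nets distributed during the 2016–2017 universal LLIN campaign".

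**The concern.** Attrition is a property of nets: of those handed out, how many are gone. The Table 2 indicator answers a different question, namely whether a household has any campaign net left. The two differ in both directions:

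- **Partial loss is invisible.** A household issued three nets that has kept one scores the same as a household that has kept all three.
- **Non-receipt looks like loss.** A household that was missed in the distribution scores the same as one whose nets have all worn out. The Discussion accepts that distribution may have been imperfect.

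No other outcome in Table 2 fills the gap. The average number of LLINs per household and the one-per-two-residents indicator are not specific to campaign nets and have no received-net baseline. Because each round samples households afresh, there is no household cohort from which loss could be followed.

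At stake is how net retention is reported by net type or over time. It also bears on the durability results: those nets are drawn from households that still have one, so the hole index describes surviving nets only, and a net-level loss figure is needed to read it properly.

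Separately, the campaign label inside an outcome definition and a sampling rule disagrees with the campaign described everywhere else.

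**Working it through.** The article gives no survivorship figure, so there is none to reproduce. The check compares what the indicator would read with true net survival.

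**Inputs from the article**
- Nets due, *n*: residents divided by 2, rounded up (LLIN distribution). Three or four residents give *n* = 2, five or six give *n* = 3, and seven or eight give *n* = 4.
- Survey households need an adult and a child aged 2–10 (Recruitment and enrolment), so they have at least two residents.
- Indicator: at least one campaign net present (Table 2).

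**Assumptions, not in the article**
- Net survival *s* is 80% in one group and 60% in another. These could be two net types or two survey rounds.
- Losses within a household are either independent or, at the other extreme, fully correlated (all kept or all lost).
- Every household received its nets, except in the last step.

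**Formulas**
- Independent loss: indicator = 1 − (1 − *s*)^*n*.
- Fully correlated loss: indicator = *s*.
- Net-level ratio (nets present / nets received): *s* in either case.

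| Case | *s* = 80% | *s* = 60% | Difference |
|---|---|---|---|
| *n* = 2, independent | 1 − 0.2² = 96.0% | 1 − 0.4² = 84.0% | 12.0 points |
| *n* = 3, independent | 1 − 0.2³ = 99.2% | 1 − 0.4³ = 93.6% | 5.6 points |
| *n* = 4, independent | 1 − 0.2⁴ = 99.8% | 1 − 0.4⁴ = 97.4% | 2.4 points |
| any *n*, fully correlated | 80.0% | 60.0% | 20.0 points |
| net-level ratio | 80.0% | 60.0% | 20.0 points |

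**Non-receipt.** If a share *r* of households received any campaign net, the indicator becomes *r* × [1 − (1 − *s*)^*n*]. Take *n* = 3, independent loss and *r* = 0.90 (assumed):
- *s* = 0.9: 0.90 × 0.999 = 89.9%
- *s* = 0.5: 0.90 × 0.875 = 78.7% (78.75% before rounding)

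With full receipt, losing half of all nets gives 87.5%. So 10% non-receipt with little loss (89.9%) and full receipt with half the nets lost (87.5%) look almost the same.

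**Dates, side by side.** The campaign evaluated is 2017–2018, with delivery from March 2017 to March 2018 (Background, Study design, Trial status). Table 2 and the durability section say 2016–2017. Taken literally, that label leaves out nets handed out from January to March 2018. The article does not give the share of nets delivered in those months.

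**The case against.** **The indicator is not empty.** A reader might infer that it cannot measure net loss at all, or that the four net types cannot be ranked on survival. The article does not support either reading. The indicator does register a household losing every campaign net, and the other net-count indicators, set against the allocation formula, give partial information. Nor does the article state a between-type hypothesis on survival; the objective is to assess it.

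**The compression depends on assumptions.** The article gives no household-size distribution and no survival rate. If households tend to lose their nets together, for instance by moving or giving them away, the indicator approaches true survival and the full 20 points appear. No single figure for the loss of contrast can be defended, which is why a range is given.

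**The full protocol may hold more.** An article condenses, and the follow-up questionnaire may already collect nets received. That would ease the remedy, but Table 2 is a table of outcome definitions and it fixes survivorship in this form. The point rests on what is stated there, not on an omission.

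**The date label is close to clerical.** The durability section samples 100 nets per study arm one year after distribution, so the study nets are almost certainly meant. A reader might infer that nets delivered in 2018 will in practice be left out, or that the 60 clusters of the last wave would be hit hardest. The first does not fit that context. The second needs delivery dates by wave, which the article does not give.

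What stands is the mismatch between the promised attrition measure and the defined indicator, and a label that needs correcting.

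**Conclusion.** The concern holds. Table 2's survivorship outcome measures household coverage with campaign nets. It understates partial loss and mixes non-receipt with loss, so it does not deliver the attrition measure that the secondary objective promises.

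For an assumed true contrast of 80% against 60%, it would show about 6 points (three nets, independent loss), 12 points (two nets, independent loss) or up to 20 points (fully correlated loss), and less than 6 for larger households under independence. The direction of the compression follows from the definition; its size rests on the assumed survival values, on nets per household, and on how losses cluster.

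The 2016–2017 label is an inconsistency to reconcile, with no shown effect on conduct. Neither matter touches the primary outcome or its analysis.

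**What to change.** - Keep the household indicator in Table 2, renamed as campaign-net coverage.
- Define survivorship as campaign nets still present divided by campaign nets received, among households that received at least one. Report the proportion of households that received none separately.
- Derive it from the campaign-net questions in the follow-up questionnaire if these record nets received. If not, add one count item for any survey round still to be done.
- Reconcile the 2016–2017 label in Table 2 and in LLIN durability and bio-efficacy with the 2017–2018 campaign and its delivery dates of March 2017 to March 2018.

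**Cost.** This means a change of wording and at most one extra question. There are two downsides. Nets received would rest on household recall. And rounds already completed would have no data if the item was not asked: follow-up began in September 2017, the article appeared in June 2019, and the last round was due to finish in September 2019, so a new item might reach only the remaining 18-month surveys. For rounds without the item, the household indicator can still be reported, described as coverage.

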#### Statistical methods

All data will be analysed on the basis of intention-to-treat and per-protocol analyses. Intention-to-treat analyses will include the assigned treatment arms and results from all clusters. For per-protocol analyses, clusters will be grouped by treatment arm according to the type of LLINs actually received in the national campaign. For clusters with mixed LLIN distribution, the number of nets from the dominant type received (numerator) will be divided by the total number of the four study net types received in that cluster, excluding non-study nets (denominator). To be included in the per-protocol analyses, the proportion of the dominant net received in the cluster must be > 75% out of the four study net types. Clusters in which the dominant net type received is ≤ 75% will be excluded from the per-protocol analyses. The primary outcome will be the prevalence of asexual parasitaemia from the cross-sectional surveys. An individual-level approach to the analysis will be used due to the large number of clusters per arm. For comparison of the primary outcome between treatment arms, generalized linear Poisson models with a log-link function will be used to allow for within-cluster correlations adjusting for baseline cluster-level parasite prevalence. The effect of the intervention will be quantified by calculation of a prevalence ratio. Separate analyses will be performed using data from the post-distribution cross-sectional surveys (performed 6, 12, and 18 months after the delivery of the nets).

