### Primary objective and hypothesis

We address the following research question: ‘Are combination LLINs (with PBO) more effective than conventional LLINs (without PBO) for malaria control in Uganda, an area with high-level P450-based pyrethroid resistance?’ We will test the hypothesis that parasite prevalence will be lower in intervention clusters (health sub-districts randomised to receive PBO nets) than in control clusters (health sub-districts randomised to conventional nets) and undertake a sub-group analysis stratified by region (Eastern and Western regions).

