### Assignment of interventions

#### Initial randomisation and net allocation

The randomisation was carried out by a member of the study team based outside of Uganda who was not directly involved in the field work. The total number of LLINs available for the four types of nets (corresponding to the four study arms) and the estimated number of LLINs needed for each health sub-district were established prior to the randomisation (Table 1). Given the restriction on the number of nets to be distributed in each study arm, adaptive randomisation was applied using the following steps: 1) A random number between 0 and 1 was generated for each cluster using STATA (StataCorp, Texas, USA). 2) Cumulative probability ranges were generated for each of the four types of net based on the targeted number of each individual type of net/targeted number of total nets. 3) The first cluster was assigned to their intervention based on which cumulative probability range the corresponding random number fell into. 4) Step 2 above was repeated after removing the number of targeted nets assigned to the cluster for the corresponding type of net and the total number of nets. 5) The next cluster was assigned to their intervention based on which revised cumulative probability range the corresponding random number fell into. 6) This process was repeated until all clusters were allocated to an intervention. The process was stratified by region, with 66 clusters in the Western region and 38 clusters in the Eastern region since although insecticide resistance is very well characterised in Eastern Uganda, little is known about patterns in the West [17, 29–31]. Areas scheduled to receive IRS with pirimiphos-methyl (Actellic) were excluded [22]. Given the nature of the trial, allocation of the LLINs was not blinded.

**Table 1 Tab1:** Revised study interventions, target number of nets, and final number of clusters allocated

Type of LLIN	Targeted total number of nets for distribution		Cumulative number of nets allocated		Number of clusters (health sub-districts) allocated				
	Original randomisation	Final randomisation	Original randomisation	Final randomisation	Waves 2 and 3	Wave 4	Western region	Eastern region	Total
PermaNet 2.0	3,217,360	3,743,320	3,220,280	3,830,280	16	21	24	13	37
PermaNet 3.0 (contains PBO)	4,100,000	3,570,640	4,101,840	3,515,520	18	14	16	16	32
Olyset Net	650,000	1,244,400	651,240	1,239,640	4	11	11	4	15

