#### Revised randomisation and net allocation

Distribution of LLINs in the first 44 clusters was completed by the Ministry of Health as scheduled, with nets distributed in 24 PBO and 20 non-PBO clusters (Table 1). However, the number of nets distributed initially was greater than estimated, resulting in a deficit of nets available for the final round of distribution within the study area. After determining the total number of nets available, the 60 remaining clusters were re-randomised, using the same process of adaptive randomisation described above, such that the number of clusters assigned to the two study arms (PBO versus non-PBO) balanced, with 52 clusters assigned to each of the two study arms in a 1:1 ratio (Table 1).

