## Discussion

The WHO has issued a preliminary endorsement of PBO LLINs based on the results of a single trial conducted in Tanzania, but additional evidence of the effect of PBO LLINs is urgently needed. Uganda, with its persistently high burden of malaria and widespread pyrethroid resistance, is an optimal setting to undertake this evaluation. We have leveraged resources by applying a cluster-randomised design to a national LLIN distribution campaign aiming to achieve universal coverage of LLINs in Uganda. Although this study design, linking the evaluation to the national LLIN campaign, presents substantial opportunities, it also presents a few limitations. Because the nets were procured in advance of establishing the trial, the type and number of nets were already fixed. Thus, we were required to use adaptive randomisation to accommodate for the differences in net availability. The shortage of nets available for the final round of distribution in the study area forced the Ministry of Health to source additional nets; as a result, the research team had to re-randomise the final 60 clusters. Moreover, the Ministry of Health and partners, not the research team, were responsible for distributing the nets. Although we worked closely with the Ministry of Health to ensure that the LLINs were allocated according to the randomisation list, there is a chance that the net distribution was imperfect. Despite these challenges, this innovative trial design demonstrates how policy makers, programme implementers, and researchers can work together to generate robust scientific evidence on the impact of malaria control interventions delivered at a national level.

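### The per-protocol rule requires more than 75% of a single net product although the primary comparison pools products by PBO class, and it leaves non-study nets out of the denominator with no cap

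*Protocol article*

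**What the plan says.** The primary hypothesis is that "parasite prevalence will be lower in intervention clusters (health sub-districts randomised to receive PBO nets) than in control clusters" given conventional nets. Both brands are pooled on each side. The section on the revised randomisation uses the same two-arm structure: the second randomisation, of the last 60 clusters, was done "such that the number of clusters assigned to the two study arms (PBO versus non-PBO) balanced". Each side ended up having 52.

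Randomisation itself was to products. Under Study design, "Clusters were randomly assigned to receive one of four types of LLINs, including two LLINs with PBO", and the section on the initial randomisation speaks of "four types of nets (corresponding to the four study arms"). The article therefore uses *study arm* in two senses, four products and two classes.

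The Statistical methods section opens with "All data will be analysed on the basis of intention-to-treat and per-protocol analyses", so the per-protocol rule also governs the primary comparison. For a cluster with mixed delivery, the numerator is the count of the dominant product. That count is "divided by the total number of the four study net types received in that cluster, excluding non-study nets (denominator"). A cluster is kept if the share is above 75% and excluded if it is 75% or less. The article gives no separate rule for the pooled comparison and no limit on the share of non-study nets.

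**The concern.** The rule has two features that do not suit the pooled comparison.

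- **Numerator.** It counts one product, while the contrast is between classes. A cluster whose nets all belong to one class can be excluded because they came from two manufacturers.
- **Denominator.** It ignores non-study nets. Such nets lower the PBO share of what was delivered but never change whether the cluster is included.

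The first costs clusters, and so precision, in the pooled per-protocol estimate. The second means that the 75% threshold does not guarantee the exposure it appears to guarantee. The article states the numerator, denominator and threshold in full, so this is a question about a rule that has been fixed and not about detail left to an analysis plan.

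**Working it through.** **Inputs.** The rule and threshold come from Statistical methods and the four products from Study design. There are 52 clusters per arm (Revised randomisation and net allocation). Sample size calculations gives control prevalence 40%, between-cluster coefficient of variation 0.3, prevalence ratio 0.83, and 10,400 children in 104 clusters, which is 100 per cluster. All net mixes below are assumed, because the article gives no delivery counts.

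**Step 1: the plan's own power figure.** With p0 = 0.40, p1 = 0.83 × 0.40 = 0.332, m = 100 and k = 0.3, the Hayes–Bennett formula is

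c = 1 + (1.96 + 0.84)² × [p0(1−p0)/m + p1(1−p1)/m + k²(p0² + p1²)] / (p0 − p1)²

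The bracket is 0.00240 + 0.00222 + 0.02432 = 0.02894, and the squared difference is 0.068² = 0.004624. This gives c = 50.1 clusters per arm. Power with 52 per arm is 81.5%, which agrees with the stated 80%.

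**Step 2: the numerator.** Share = largest single product / total of the four study products, kept if above 75%.

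| Study nets (per 100) | Share by the rule | Decision | Share of the majority class |
|---|---|---|---|
| 100 PermaNet 3.0 | 100% | kept | 100% PBO |
| 60 PermaNet 3.0, 40 Olyset Plus | 60% | excluded | 100% PBO |
| 75 PermaNet 3.0, 25 Olyset Plus | 75% | excluded | 100% PBO |
| 50 PermaNet 3.0, 30 Olyset Plus, 20 PermaNet 2.0 | 50% | excluded | 80% PBO |
| 60 PermaNet 2.0, 40 Olyset Net | 60% | excluded | 100% non-PBO |

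The last four would all be kept if the 75% threshold were applied to the class share.

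**Step 3: the denominator.** Take 80 PermaNet 3.0, 20 PermaNet 2.0 and N non-study nets, and assume that the non-study nets carry no PBO. The rule gives 80/100 = 80% and keeps the cluster for every N. The PBO share of all nets is 80/(100 + N):

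- N = 6: 80/106 = 75.5%
- N = 7: 80/107 = 74.8%, below the trial's own threshold
- N = 25: 64%
- N = 100: 40%

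A cluster whose study nets are all PermaNet 3.0 is more robust: 100/133 = 75.2% and 100/134 = 74.6%, so it takes 34 non-study nets per 100 study nets to cross the line. Under the same assumption, non-study nets do not weaken a conventional cluster's class. With 80 PermaNet 2.0, 20 PermaNet 3.0 and 7 non-study nets, the non-PBO share is 87/107 = 81.3%.

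**Step 4: cost of lost clusters.** One cluster is 1/52 = 1.9% of an arm. If clusters were lost equally from both arms, the Step 1 formula gives, at a prevalence ratio of 0.83, power of 77.4% with 47 per arm and 72.6% with 42. These losses are assumptions that show the slope; they are not estimates.

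**The case against.** The case for leaving the rule alone has real weight.

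- **Mixed-brand clusters are not fully compliant.** A reader might infer that the rule discards clusters that followed their allocation. The documents do not support that. Clusters were randomised to one of four products, and a cluster assigned PermaNet 3.0 that received 40% Olyset Plus did not receive its allocation. The Background says that the nets differ in insecticide, concentration, weight and construction. A product-purity rule is a defensible per-protocol definition, and it fits the brand comparisons under Secondary objectives and hypotheses. This stands. It does not make the rule the best one for a contrast that pools the brands by design.
- **Shortage is not evidence of non-study nets.** The Discussion says that the deficit "forced the Ministry of Health to source additional nets", and a reader might take this to mean that other brands reached the trial clusters. Table 1 points the other way: the target for the four study products rose from 8,967,360 to 10,159,920, and the final allocation of 10,159,920 consists of study products only. What remains is the rule's own provision for mixed delivery and non-study nets, and the Discussion's admission that distribution may have been imperfect. That shows possibility, not scale.
- **Lost precision is not bias.** A reader might conclude that the per-protocol estimate no longer measures the effect of PBO nets. Dropping mixed-brand clusters does not show that, since every cluster kept as PBO still has more than 75% of one PBO product among its study nets. Only the denominator can misstate exposure, and only to the extent that non-study nets were delivered.

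**Conclusion.** The point holds as a mismatch between a product-level rule and a class-level comparison, together with an uncapped denominator. Within-class mixes in which neither brand exceeds 75% are excluded from the pooled per-protocol comparison without need. A cluster can also fall below 75% PBO among all delivered nets and still be kept as PBO. In the worked case, 7 non-study nets per 100 study nets are enough.

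The reach is limited. Clusters that received a single PBO product are kept. Intention-to-treat uses all clusters and is unaffected, so nothing here touches the main result. The number of affected clusters is not given and could be zero. The net mixes, the assumption that non-study nets carry no PBO, and the cluster losses in the power figures are illustrations and do not come from the article.

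**What to change.** Replace the single rule with two.

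- **PBO versus non-PBO.** Group each cluster by its majority class. Include it if that class (PBO, or non-PBO) makes up more than 75% of the nets delivered there.
- **PermaNet 3.0 versus 2.0, and Olyset Plus versus Olyset Net.** Keep the single-product rule at more than 75%.

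Where counts of non-study campaign nets are available, include them in the denominator by PBO status, or report the result with them included as a sensitivity analysis. State how many clusters each rule excludes, by arm.

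The cost is about two sentences. The class share uses the same delivery counts that the present rule already needs. The downsides are small: brands are mixed within each pooled class, and the number and PBO status of non-study nets must be obtained, which the article does not say is recorded. Distribution ended in March 2018, so a rule changed now could be influenced by known delivery data. The change should be dated, made before the outcomes are compared by arm, and reported beside the result under the present rule.
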